### Interventions

2.3

All patients will receive the standard care for CRF as recommended by the Oncology Branch of the Chinese Medical Association (24). The specific regimen will include: 1) Psychological support: imparting knowledge on breast cancer recovery and CRF, and engaging in weekly therapeutic communication with the patients, each session lasting approximately 2 hours, to assist in managing adverse emotions; 2) Nutritional management: conducting a nutritional risk assessment once a week using the Nutritional Risk Screening 2002 (NRS 2002) tool, with patients identified at nutritional risk being referred to the nutritional department for specialized treatment; 3) Sleep management: overseeing the establishment and maintenance of regular sleeping schedules and environments conducive to sleep, with pharmacological treatment being administered as necessary; 4) Exercise guidance: supervising patients to partake in 180 to 300 minutes of moderate-intensity physical activities per week, such as brisk walking, yoga, and Tai Chi. During the study, the use of treatments outside the study protocol for CRF will be prohibited (e.g., stimulants or corticosteroids).

The TFM group will receive TFM therapy. The moxa sticks used for the treatment are produced by Chongqing Zhao’s Thunder-Fire Moxibustion Traditional Medicine Research Institute in China, each measuring 2.8 cm in diameter, 10.5 cm in length, and weighing 230 g. TFM will be carried out by four female acupuncturists, each with more than three years of experience in moxibustion therapy and holding a professional license. The acupoints for treatment will include CV6 (Qihai), CV4 (Guanyuan), SP6 (Sanyinjiao), and both sides ST36 (Zusanli). The acupuncturists will manipulate a lit moxa stick, moving it up and down at a vertical distance of 2-3cm from the skin over the acupoints for 30 minutes, inducing a sensation of deep tissue warmth without causing any burn pain. The treatment frequency will be every other day for 30 days, totaling 15 sessions. The WC group is scheduled to commence TFM therapy following the conclusion of the study.

### Outcomes

2.4

#### Primary efficacy outcome

2.4.1

The primary efficacy outcome is the change in the total fatigue score on the PFS at the end of a 30-day treatment period relative to baseline. The PFS is a well-validated, multidimensional tool used to assess the severity of CRF and is highly sensitive to fluctuations in fatigue levels over time (14). It has been widely utilized in clinical trials assessing CRF interventions in breast cancer survivors (25, 26) thereby enhancing the external validity and comparability of our study results. The PFS consists of 22 rating items, which are divided into four subdomain scales: behavioral fatigue (6 items), emotional fatigue (5 items), sensory fatigue (5 items), and cognitive fatigue (6 items), with each item scored on a scale from 0 to 10. The total fatigue score is the average of these 22 items, with severity categorized as mild (1-3 points), moderate (4-6 points), and severe (7-10 points). Assessments are conducted at baseline, on days 10, 20, and 30 (end of treatment), and on day 60 (end of follow-up).

#### Secondary efficacy outcomes

2.4.2

The critical secondary efficacy endpoints include changes in total fatigue scores at all other measurement time points (day 10, day 20, and day 60) compared to baseline, as well as changes in the four subdomain fatigue scores at all time points (day 10, day 20, day 30, and day 60) relative to baseline. Another secondary endpoint is the quality of life, which will be assessed using the KPS. The KPS ranges from 0 to 100, with higher scores indicating a better quality of life.

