## Introduction

1

The National Comprehensive Cancer Network defined cancer-related fatigue (CRF) as “a distressing, persistent, subjective sense of physical, emotional, and/or cognitive tiredness or exhaustion related to cancer or cancer treatment that is not proportional to recent activity and interferes with functioning” (1). Recognized as one of the most common and burdensome symptoms, CRF affects over half of all cancer patients (2). According to the latest data from GLOBOCAN 2020, breast cancer, with an estimated 2.3 million new cases, has overtaken lung cancer as the most frequently diagnosed cancer worldwide (3). Notably, CRF is more prevalent among patients with breast cancer, showing a higher incidence rate than in other cancer types (4). Over 90% of breast cancer patients experience CRF during or after treatment (5, 6), and approximately one-third of these patients suffer from moderate to severe levels of CRF (7). Current treatment options for CRF include primarily pharmacological and non-pharmacological schemes (8). Non-pharmacological treatments, including exercise, psychological support, cognitive-behavioral therapy, and sleep management, are the mainstay, yet their efficacy is often limited. Pharmacological treatments typically involve stimulants and corticosteroids, yet their use is often limited due to associated side effects. Consequently, the imperative to explore and implement new strategies to alleviate CRF in breast cancer patients, with the goal of improving their quality of life, has become a critical area of concern.

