#### Inclusion criteria

2.2.2

(1) Meets the International Classification of Diseases, 10th Revision (ICD-10), diagnostic criteria for CRF;(2) Moderate to severe fatigue, defined as a score of ≥4 on the PFS;(3) Diagnosed with stage I-III breast cancer in women;(4) Age between 18 and 80 years old;(5) Karnofsky Performance Status (KPS) score of ≥70;(6) Completion of breast cancer treatment (surgery, radiotherapy, chemotherapy, targeted therapy) at least 12 weeks prior, but ongoing endocrine therapy exceeding 4 weeks is allowed.

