### Sample size

2.7

The sample size was calculated based on the primary efficacy outcome, using data from a preceding pilot study. At the end of the 30-day treatment period, total fatigue scores in the TFM and WC groups decreased by 1.93 ± 0.47 and 0.94 ± 0.35 points, respectively, compared to baseline. The sample size calculation was conducted using the “Two-Sample T-Tests for Superiority by a Margin Allowing Unequal Variance” module in PASS software (version 15.0). Assuming a 20% dropout rate, a one-sided α of 0.025, a statistical power (1-β) of 0.99, and a superiority margin of 0.5, it was determined that at least 35 patients should be allocated to each group. Since the primary efficacy outcome will be analyzed using a linear mixed model, which offers greater statistical power than the traditional two-sample t-test (28), the larger sample size derived from the t-test calculation will further enhance the robustness and reliability of the analysis.

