### Statistical analysis

2.9

All analyses will be conducted within the intention-to-treat population, encompassing all randomized participants. For continuous variables, data adhering to a normal distribution will be expressed as mean ± standard deviation, while non-normally distributed data will be presented using the median and interquartile range. The Shapiro-Wilk test will be used to determine the normality of the data. Categorical variables will be depicted as frequencies and percentages. The planned statistical analyses will be conducted using SPSS software (version 28.0) and the R programming language (version 4.3.1). Significance testing will be bilateral, with a P-value of ≤ 0.05 denoting statistical significance.

To compare the longitudinal trajectories of changes in PFS scores from baseline between groups at successive follow-up time points, linear mixed models will be employed. Given the correlation between repeated measures within the same participant, this model will include participant-specific random effects (29). The fixed effects of the model will include group, follow-up time, and the interaction between group and follow-up time (30). Covariates will include age and baseline PFS scores. No imputation of missing data is planned, as the analysis model itself accounts for missing data and remains valid under the missing-at-random assumption.

For other continuous outcome measures, such as KPS scores, HPA axis-related hormonal factors, and inflammatory markers, comparison between groups will employ analysis of covariance adjusting for baseline values if the data are normally distributed. If not, the Mann-Whitney U test will be applied. Missing data will be addressed through the application of the last observation carried forward method.

We plan to conduct predefined subgroup analyses for the primary outcome, considering the following baseline variables: age (≤55, >55), nutritional risk (no, yes), sleep disorder (no, yes), fatigue severity (moderate, severe), body mass index (≤24, >24), KPS score (70, 80, 90, 100), cancer stage (I, II, III), cancer subtype (Luminal A, Luminal B, HER2-positive, triple-negative), and cancer treatment (surgery, radiotherapy, chemotherapy, targeted therapy, endocrine therapy). Consequently, except for the primary outcome, the interpretations of other outcomes and subgroup analyses will be treated as exploratory.

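### The quality-of-life endpoint is measured only by the KPS, which the protocol itself identifies as a performance status, so its result supports no quality-of-life conclusion

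*Protocol article*

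**What the plan says.** Section 2.4.2 (Secondary efficacy outcomes) first lists the Piper Fatigue Scale (PFS) endpoints that it calls critical, then adds: "Another secondary endpoint is the quality of life, which will be assessed using the KPS". It interprets the score in the next sentence: "The KPS ranges from 0 to 100, with higher scores indicating a better quality of life".

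Section 2.2.2 (Inclusion criteria) spells out the abbreviation and sets an entry threshold: "Karnofsky Performance Status (KPS) score of ≥70". Section 2.9 (Statistical analysis) lists the baseline subgroups for this variable as "KPS score (70, 80, 90, 100", four levels in all.

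For the KPS and the other continuous outcomes, Section 2.9 says that "comparison between groups will employ analysis of covariance adjusting for baseline values if the data are normally distributed", with a Mann-Whitney U test otherwise. It closes by saying that "except for the primary outcome, the interpretations of other outcomes and subgroup analyses will be treated as exploratory".

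Apart from Section 2.4.2, quality of life appears only in the Introduction, where new strategies against cancer-related fatigue are sought "with the goal of improving their quality of life".

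**The concern.** The protocol gives one score two meanings. For eligibility it is a performance status; for efficacy it becomes quality of life. The article offers no argument or evidence for the second reading. By contrast, Section 2.4.1 justifies the PFS as validated, multidimensional and sensitive to change. No other instrument is named that could carry a quality-of-life claim.

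What is at stake is the label on a published result. If the plan is followed as written, a difference in KPS would be reported as an effect on quality of life, and the absence of one as no such effect. Because the Introduction gives quality of life as the reason for seeking new treatments, readers are likely to look for that result.

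**Working it through.** **1. The plan's own figure.** No sample size, effect or standard deviation is stated for the KPS. The only calculation, in Section 2.7, is for the PFS, where pilot scores "decreased by 1.93 ± 0.47 and 0.94 ± 0.35 points, respectively, compared to baseline". It can be reproduced:

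- Effect beyond the margin: 1.93 − 0.94 − 0.5 = 0.49.
- Variance sum: 0.47² + 0.35² = 0.2209 + 0.1225 = 0.3434.
- Two-sample unequal-variance t-test, one-sided α 0.025, target power 0.99: 28 per group gives power 0.9913, and 27 gives 0.9892. So 28 are needed.
- Allowing for 20% dropout: 28 / (1 − 0.20) = 35 per group, as stated.

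The figure is sound. It concerns fatigue only and says nothing about the KPS.

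**2. What the score is said to measure.**

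| Section | Role of the KPS | Meaning given |
|---|---|---|
| 2.2.2 Inclusion criteria | entry threshold, 70 or above | performance status |
| 2.4.2 Secondary efficacy outcomes | efficacy endpoint | quality of life |
| 2.9 Statistical analysis | baseline subgroup variable and analysed outcome | KPS score, no further meaning |

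The name and the eligibility use support a statement about performance status. Only the two sentences in Section 2.4.2 support the quality-of-life reading, and they assert it without grounds. Neither the choice of test nor a larger sample would change what the score measures.

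**3. Room to improve (supporting point only).** The inputs are the entry threshold of 70, the four baseline levels in Section 2.9 and the scale maximum of 100 in Section 2.4.2. Room to improve = 100 − baseline:

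| Baseline KPS | Largest possible gain |
|---|---|
| 70 | 30 |
| 80 | 20 |
| 90 | 10 |
| 100 | 0 |

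A participant entering at 100 cannot improve, and one entering at 90 can rise by one listed level. The plan allows for participants at 100, since it makes them a subgroup. Adjusting for baseline does not create headroom.

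The resulting loss of sensitivity depends on how many participants enter at each level, and the documents give neither a KPS distribution nor a standard deviation. The entry criteria point both ways. Participants finished surgery, radiotherapy, chemotherapy and targeted therapy at least 12 weeks earlier, but all have a PFS score of 4 or more and may be on endocrine therapy. The loss therefore cannot be calculated.

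**The case against.** The strongest reply is that little hangs on this endpoint. The KPS stands outside the secondary endpoints called critical, Section 2.9 treats every non-primary outcome as exploratory, and the stated aims in Section 2.1 are efficacy, safety and mechanisms, not quality of life. This is correct and keeps the point minor. It does not remove it: exploratory status limits how strongly a result may be read, not what the score measures.

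A reader might also go further and infer that the threshold of 70 makes the endpoint useless: that the 0 to 100 range no longer applies, or that a null result would tell us nothing. The documents do not support this. The threshold restricts entry values, and the four levels in Section 2.9 are baseline subgroups. Nothing prevents a score below 70 at follow-up, and participants entering at 70, 80 or 90 can improve. The groups can separate in either direction, so a null result remains informative about performance status, though less sensitive to benefit. Any stated share of participants at 100 would be a guess.

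Nor does the article say who assigns the KPS score. The argument needs no assumption about that, since it rests on the name and uses the protocol gives the scale.

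Finally, adding a questionnaire is partly a matter of preference, and it has its own weakness. Participants know their allocation (Section 2.8), so self-reported quality of life would be open to expectation bias. This stands, and it is why the questionnaire is only an option.

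**Conclusion.** The concern holds as a mislabelled construct. Section 2.4.2 reads a performance-status score as quality of life, and the article names no other instrument for that purpose. A KPS result would support a statement on performance status and none on quality of life. This follows from the protocol's own wording and needs no numerical assumption.

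Limited headroom is a secondary weakness: 0 to 30 points depending on the baseline level, with an unknown effect on sensitivity and no restriction on deterioration. It does not show that the endpoint is uninformative.

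Severity is minor. The primary PFS outcome, its analysis and the 35 per group are untouched.

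**What to change.** In Section 2.4.2, rename the endpoint 'performance status (KPS)', delete the two statements that equate it with quality of life, and add that no quality-of-life conclusion will be drawn from it. This costs nothing in participants, visits or power; it gives up only a claim that the instrument does not support. A sentence noting the limited room for improvement at baseline would help readers interpret the result.

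Optionally, if a quality-of-life claim is wanted, add one validated self-completed questionnaire at visits that already take place, such as baseline, day 30 and day 60. The cost is a small added burden on participants. The plan should then acknowledge that self-report in this open-label waitlist design carries expectation bias.

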#### Mechanism outcomes

2.4.3

To investigate the underlying mechanisms of action of TFM, this study will collect blood and fecal samples from all participants at baseline and after a 30-day treatment period. Fasting blood samples will be collected between 7:00 AM and 9:00 AM, and the levels of serum HPA axis-related hormones, including adrenocorticotropic hormone (ACTH), corticotropin-releasing hormone (CRH), and cortisol (CORT), as well as serum inflammatory markers, including interleukin-6 (IL-6) and interleukin-8 (IL-8), will be assessed using enzyme-linked immunosorbent assay (ELISA). The gut microbiota in fecal samples will be analyzed through 16S rRNA gene sequencing. Furthermore, untargeted metabolomics analyses of serum and fecal samples will be performed using liquid chromatography-mass spectrometry (LC-MS) technology. A variety of bioinformatics approaches will also be employed for in-depth analysis of the data, including but not limited to alpha and beta diversity analysis, principal component analysis (PCA), principal coordinates analysis (PCoA), non-metric multidimensional scaling (NMDS), linear discriminant analysis effect size (LEfSe), and partial least squares discriminant analysis (PLS-DA).

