### Study design

2.1

The study is designed as a prospective, single-center, open-label, parallel-group, randomized controlled clinical trial. It aims to evaluate the efficacy and safety of TFM treatment in breast cancer survivors with CRF and to preliminarily explore its potential mechanisms. The study duration is 65 days, including a 5-day screening period, a 30-day treatment period, and a 30-day follow-up period. We plan to enroll 70 participants at the Hospital of Chengdu University of Traditional Chinese Medicine, who will be randomly assigned in a 1:1 ratio to either the waitlist control (WC) group or the TFM group. During the 30-day treatment period, all patients will receive standard care. Patients in the TFM group will receive additional TFM treatment every other day, for a total of 15 sessions. The primary outcome measure is the change in the total fatigue score on the PFS at the end of treatment compared to baseline. The study flow is illustrated in **Figure 1**.

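### The only significance rule, an unadjusted two-sided P ≤ 0.05, has no exception for the 16S and untargeted metabolomic features (minor)

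*Protocol article*

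**What the plan says.** Section 2.4.3 (Mechanism outcomes) of the protocol article plans to "collect blood and fecal samples from all participants at baseline and after a 30-day treatment period". Five serum hormones and cytokines are measured by ELISA. Three high-dimensional platforms are added. For the first, "The gut microbiota in fecal samples will be analyzed through 16S rRNA gene sequencing". The other two are serum and fecal metabolomics: "untargeted metabolomics analyses of serum and fecal samples will be performed using liquid chromatography-mass spectrometry (LC-MS) technology". An open-ended list of bioinformatic methods follows, which includes LEfSe and PLS-DA.

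Section 2.9 (Statistical analysis) sets one criterion for the whole trial: "Significance testing will be bilateral, with a P-value of ≤ 0.05 denoting statistical significance". It names no multiplicity or false discovery rate control. The same section closes by saying that "except for the primary outcome, the interpretations of other outcomes and subgroup analyses will be treated as exploratory". Section 2.1 (Study design) describes the mechanism aim in similar terms: "to preliminarily explore its potential mechanisms".

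**The concern.** A per-test threshold of 0.05 suits a handful of outcomes. It does not suit screening of hundreds or thousands of features, where the number of false labels grows in proportion to the number of features with no treatment effect. Section 2.9 makes no distinction between the two situations. LEfSe, which section 2.4.3 names, screens features one at a time between groups, so feature-level significance calls are a foreseeable output.

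What is at stake is the mechanism part of the trial. The Abstract gives underlying mechanisms as one of the study's aims. The Discussion motivates the work with claims about individual features, such as one bacterial genus and one bile acid. A list of taxa and metabolites called significant at raw P ≤ 0.05 could be read the same way, with no indication of how much of it is noise.

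**Working it through.** **Inputs from the protocol.** Two-sided threshold 0.05 (section 2.9). 35 patients per arm and 20% dropout (section 2.7), so 35 × 0.8 = 28 per arm with complete data. Allocation 1:1 (section 2.1).

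**Inputs that are assumptions.** The number of features M, the proportion π₁ of features that TFM truly changes, and the standardized effect on those features. The protocol gives none of these.

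**Step 1: the protocol's own figure.** The mechanism outcomes have no calculation. The sample size for the primary outcome is the only derived figure, and it supplies the arm sizes used below. Difference less margin: 1.93 − 0.94 − 0.5 = 0.49. With SDs 0.47 and 0.35, one-sided α 0.025 and power 0.99, the unequal-variance t-test needs 28 per arm (power 0.991). Then 28 / 0.8 = 35, as stated.

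**Step 2: expected false positives if no feature changes.** Expected count = 0.05 × M. This holds whether or not the features are correlated.

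| M (assumed) | Expected false positives |
|---|---|
| 100 | 5 |
| 500 | 25 |
| 1,000 | 50 |
| 5,000 | 250 |
| 10,000 | 500 |

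For 100 independent features, the chance of at least one is 1 − 0.95^100 = 0.994.

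**Step 3: share of labelled features that is false.** Expected share ≈ 0.05(1 − π₁) / [0.05(1 − π₁) + power × π₁]. Per-feature power from the two-sample t-test at two-sided 0.05:

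| Per arm | Effect 0.5 SD | Effect 0.8 SD |
|---|---|---|
| 28 | 0.451 | 0.836 |
| 35 | 0.541 | 0.910 |

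Over these four settings:

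| π₁ (assumed) | False share, lowest to highest |
|---|---|
| 1% | 0.845 to 0.916 |
| 5% | 0.511 to 0.678 |
| 10% | 0.331 to 0.499 |
| 20% | 0.180 to 0.307 |
| 30% | 0.114 to 0.205 |
| 50% | 0.052 to 0.100 |

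Worked example: π₁ = 10%, 28 per arm, effect 0.5 gives 0.045 / (0.045 + 0.0451) = 0.499.

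The share passes one half when π₁ falls below 0.05 / (0.05 + power): 0.100 and 0.056 at 28 per arm, 0.085 and 0.052 at 35 per arm, for effects of 0.5 and 0.8 SD respectively. A Benjamini-Hochberg rule at 5% would hold the expected false share to about 5% whatever π₁ is, under its usual dependence conditions.

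**Step 4: why PLS-DA plots need a validation figure beside them.** Two-component PLS-DA was fitted to pure noise with 28 or 35 per arm and 500, 2,000 or 5,000 features, 20 runs per setting. In-sample accuracy was 100% in every setting, and R²Y was 0.98 to 1.00. Seven-fold cross-validated accuracy was 0.49 to 0.53, which is chance. At this sample size, in-sample separation alone says nothing about a treatment effect.

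**The case against.** The best defence is that this is a condensed article. False discovery rate procedures and omics pipelines are commonly left to a fuller plan. The 0.05 criterion may be only a general convention, and an FDR-adjusted P ≤ 0.05 would be compatible with it. The tests spelled out in section 2.9 are illustrated with KPS, hormones and inflammatory markers, not with taxa or metabolites, and several of the listed methods are ordinations that test no individual feature. The mechanism work is declared exploratory and preliminary.

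Much of this stands, and it rules out several stronger readings:

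- **That PLS-DA is planned without validation.** Section 2.4.3 neither describes nor excludes cross-validation or permutation testing, and its list is open. Step 4 shows the danger of an unvalidated fit, not that one is planned.
- **That the baseline samples will go unused.** The section does not say whether day-30 values, changes or another contrast enter LEfSe and PLS-DA.
- **That the mechanism results will be mostly false.** Step 3 gives a false share from about 5% to 92%. A majority requires that fewer than about 5% to 10% of features truly change, and the protocol says nothing on that.
- **That P ≤ 0.05 should be kept for the primary outcome alone.** That would also remove the threshold from KPS, the hormones, the cytokines and the fatigue subdomains, for which the argument here gives no reason.

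What the defence does not remove is the stated rule. It is general, carries no exception, and says what denotes significance. The exploratory label governs interpretation and leaves the labelling of features as it was.

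**Conclusion.** The point holds as a minor one. The fault lies in a rule worded too broadly, not in the article's silence on omics detail. Followed literally, it calls about 5% of unaffected features significant: 25 to 250 per metabolomic matrix on the assumption of 500 to 5,000 features with none changed. The share of false findings among those called cannot be fixed from the document. The error rate of the primary outcome, the sample size and the efficacy conclusion are untouched. Severity is minor because every outcome other than the primary is already declared exploratory.

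**What to change.** In section 2.9, exempt the omics features from the flat P ≤ 0.05 rule. State that within each platform (16S, serum metabolomics, fecal metabolomics) a feature is called significant only at a Benjamini-Hochberg false discovery rate of 5%, from a between-group comparison adjusted for that participant's baseline sample. In section 2.4.3, add that PLS-DA separation will be presented only with its cross-validated performance and a permutation test. The threshold for the other outcomes can stay as it is.

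The cost is two or three sentences and a few lines of analysis code. No new patients, visits or samples are needed, because baseline and day-30 samples are already planned for everyone. The downside is that fewer features will be called significant.
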